#### Analysis

A standard statistical software package will be used for statistical tests (parametric and non-parametric). The analysis will be both intention-to-treat (ITT) and as per-protocol (PP). All randomized participants will be included in the safety analysis. All statistical processing will be performed using standard statistical package (SPSS, BMDP, and CIA) unless otherwise stated. The data will be individually analyzed for central tendencies (mean, median), range, standard deviation and 95% confidence intervals for each intervention arm in the study. Titer data will be “log” transformed before any analyses [and GMT, GSD, etc. will be reported and will be used for testing with respect to that parameter. Data will be tabulated and graphically shown using standard format using MS Excel and other software programs. Standard parametric (Student *t*-tests–paired and unpaired, ANOVA, etc.) and non-parametric statistical tests (Wilcoxon Signed Rank test, Mann-Whitney “U” test, Kruskal-Wallis test, etc.) will be used depending upon the normality of the data, level of measurement and appropriateness/applicability. Fisher's exact test or Chi square will be used to test the proportion of participants classified as efficacy failures and those with AE. All AEs will be presented as proportion and with Wilson's recommended exact binomial 95% Confidence Interval.

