# *HR-BHF: Health Related-Habits, Behavior and Fitness*.

@ *WHO QOL BREF: World Health Organization Quality of Life Instruments-short form*.

**Table 2 T2:** Schedule of laboratory investigations.

**Visit**	**Visit 0 Screening (Day −7 to −1)**	**Visit 1 Enrollment and randomization (Day 1)**	**Visit 2 (4 wks)**	**Visit 3: (8 wks)**	**Visit 4 (12 wks)**	**Interim analysis**	**Visit 5:(16 wks)**	**Visit 6** **Intervention completion** **(24 wks)**	**Visit 7: Part 1 completion (28 wks)**
CBC: blood hemoglobin, total and differential count, platelets Erythrocyte sedimentation rate (Westergren)	X				X			X	
D-dimer	X				X			X	
LFT: serum liver enzymes-SGOT, SGPT, alkaline phosphatase Serum albumin, globulin, bilirubin	X				X			X	
RFT: blood urea nitrogen Serum creatinine	X				X			X	
Blood sugar profile (BSL fasting and HbA1c)	X				X			X	
Urine routine	X				X			X	
^+^Urine pregnancy test	X		X	X	X		X	X	X
^#^RT-PCR throat/nose swab testing for SARS-CoV2 RNA	X		X	X	X		X	X	X
SARS- CoV-2 S1, RBD and N Specific IgG		X	X	X	X		X	X	X
sVNT					X			X	X
SNT (Wuhan isolate USA-WA1/2020 and Delta variant B1.617.2)					X				X

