#### Randomization

The participants eligible for enrolment will be randomized in a 1:1 ratio to Ashwagandha + COVISHIELD^TM^ or placebo + COVISHIELD^TM^ according to a pre-specified randomization scheme prepared by a statistician (SS) using a computerized system. Block randomization specific to each clinical study site will ensure equal number of participants per group with a small block size (e.g., a block of 4–6 participants). The statistician (SS) will design the randomization schedule following computer generated random numbers. The randomization scheme will consider the subsets of participants who are receiving first and second dose.

The patient number and the treatment allocation as per the schedule will be printed on a card, which will be sealed in an opaque envelope for each patient. The envelope of each patient will be delivered to respective trial sites. The treatment allocation will be concealed. Considering the study design, it is important to have a dosage form that ensures blinding. The tablets of Ashwagandha and placebo will have identical color and weight and will be dispensed in sealed bottles. The bottles will have same color and labeling. The bottles will be specific to the participant. The participant code will be written on each bottle containing the tablets.

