#### Clinical Outcomes

##### Primary Outcome Measure

Immunogenicity as measured by SARS-CoV-2 spike (S1) and RBD-specific IgG antibody titres.

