### Statistical Analysis

#### Sample Size and Power

The sample size is calculated based on the primary objective of improved immunogenicity of the vaccine with administration of Ashwagandha. Also, it was felt important to obtain a reasonably suitable (non-probabilistic) sample size for safety and tolerability. As there was no prior data on the expected effect size of the difference between the two study groups, a superiority margin of 7% was decided by expert consensus between the biostatistician (SS) and senior authors (AC, GT, [name], and BP). The sample size was calculated with 80% power and after consideration of interim analysis at the end of 12 weeks; assuming vaccine efficacy of 80% (22). The calculated sample size with the provision of one interim analysis was rounded to 600 subjects per study arms and totalling 1,200. The study will include upto 300 participants who have received the first dose and at least 900 participants who have received the second dose.

An interim analysis is planned after completing 12 weeks of intervention. The sample size of the study is decided based on the plan of one interim analysis. The sample size for interim analysis will be minimum 300 (with alpha = 2.96%).

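### The stated rule picks the titre test by normality from a list whose between-arm tests use neither Day-1 titre, site nor dose group; separately, no primary visit or rule for the two titres is named

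*Protocol article*

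**What the plan says.** The Primary Outcome Measure section reads: "Immunogenicity as measured by SARS-CoV-2 spike (S1) and RBD-specific IgG antibody titres". It gives no visit and no rule for combining the two titres. Table 2 schedules "SARS- CoV-2 S1, RBD and N Specific IgG" on Day 1 and at weeks 4, 8, 12, 16, 24 and 28, and Table 3 agrees.

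The Analysis section says titres are log "transformed before any analyses" and that geometric means will be reported and used for testing. It then names Student t-tests ("paired and unpaired, ANOVA, etc") and the Wilcoxon signed-rank, Mann-Whitney and Kruskal-Wallis tests. These "will be used depending upon the normality of the data, level of measurement and appropriateness/applicability".

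The Randomization section says "Block randomization specific to each clinical study site will ensure equal number of participants per group" and "The randomization scheme will consider the subsets of participants who are receiving first and second dose". On the mix, Sample Size and Power says "The study will include upto 300 participants who have received the first dose and at least 900" who have received the second. That section gives a 7% margin, an assumed vaccine efficacy of 80%, 80% power, and alpha of 2.96% for the interim analysis. It gives no titre SD and no correlation with Day 1.

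**The concern.** There are two separate issues.

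**The test.** The choice among the listed tests is made after the data are seen. The listed between-arm tests (unpaired t, ANOVA, Mann-Whitney, Kruskal-Wallis) leave out a baseline value of the outcome itself and the factors built into the randomisation. First- and second-dose recipients may well have different titres, and an unadjusted test puts that spread into the error term. If normality sends the analysis to Mann-Whitney, the test no longer addresses the ratio of geometric means.

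**The endpoint.** Two titres at six post-baseline visits give 2 × 6 = 12 between-arm results. The text does not say which one, or which combination, decides the trial.

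At stake are precision that could be had without new data, a treatment effect whose definition does not depend on a pre-test, and a known false-positive rate for the main claim.

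**Working it through.** **1. The plan's own figure.** With both arms at 80%, a margin of 0.07, 80% power and 2.96% read as two-sided and applied at the final look (an assumption), n = 2 × 0.8 × 0.2 × (2.175 + 0.842)² / 0.07² = 595 per arm. That rounds to the stated 600. It is a calculation on a proportion, so it says nothing about power for a log-titre comparison. Everything below therefore uses assumed titre parameters, shown as ranges, and an assumed two-sided 5% level.

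**2. Adjusting for Day-1 titre.** The variance factor is 1 − ρ² and the equivalent size is 600 / (1 − ρ²). If the unadjusted test has 80% power, adjusted power is Φ(2.80 / √(1 − ρ²) − 1.96).

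| Assumed ρ | Variance cut | 600 per arm acts like | Power, from 80% |
|---|---|---|---|
| 0.3 | 9% | 659 | 84% |
| 0.5 | 25% | 800 | 90% |
| 0.7 | 49% | 1,176 | 98% |

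**3. Leaving out dose group.** With a 25/75 mix and a gap of d within-group SDs, the added variance is v = 0.25 × 0.75 × d². If the randomisation balances dose group, the true type I error of the unadjusted test is 2 × [1 − Φ(1.96 √(1 + v))]. Power, where the adjusted test has 80%, is Φ(2.80 / √(1 + v) − 1.96) if the arm difference really carries the extra spread. If dose group is exactly balanced, it is Φ(2.80 − 1.96 √(1 + v)).

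| Assumed d | v | Power, spread carried | Power, exact balance | True alpha |
|---|---|---|---|---|
| 0.5 | 0.047 | 78% | 79% | 4.5% |
| 1 | 0.188 | 73% | 75% | 3.3% |
| 2 | 0.750 | 56% | 58% | 1.0% |

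The direction is conservative throughout.

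**4. Both together, on the titre scale.** Pooled variance is SD² + 0.1875 × gap². Adjusted variance is SD² (1 − ρ²). Assume SD 0.5 log10, gap 0.5 log10 and ρ 0.5:
- Pooled 0.2969, adjusted 0.1875, ratio 0.63.
- Detectable GMT ratio, 10^(2.80 × √(variance × 2/600)): 1.225 unadjusted, 1.175 adjusted.
- With no gap, the unadjusted value is 1.205.

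Across SD 0.4 to 0.5, gap 0.3 to 0.7 and ρ 0.3 to 0.7, the variance ratio runs from 0.32 to 0.85.

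**5. Choosing the test by normality.** This was simulated with 600 per arm and 4,000 runs (simulation error about 0.35 points), using a Shapiro test and then t or Mann-Whitney. Type I error was 4.8% for normal log titres and 5.5% for a 25/75 mixture two SDs apart. The t-test alone gave 4.8% and 5.6% on the same data. Taking the smaller of the two p-values gave 5.6% and 6.4%.

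**6. Twelve candidate results, each tested at 5%.** If independent: 1 − 0.95¹² = 46%. Simulated with correlated results:

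| Titre correlation | Visit correlation | Any of 12 significant |
|---|---|---|
| 0.5 | 0.5 | 35% |
| 0.8 | 0.5 | 30% |
| 0.8 | 0.7 | 24% |
| 0.9 | 0.8 | 19% |
| 0.95 | 0.9 | 14% |

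**The case against.** The strongest reply is that the Analysis section is a general menu for all study data. Its lists end openly and leave room for what is appropriate, and covariates and model form are commonly settled in a SAP or full protocol that is not shown. That stands against any claim that the plan fixes an unadjusted two-group test as its primary analysis; a reader might infer this, but the text does not say it. What remains is a written rule that selects by normality from a list in which every named between-arm test is unadjusted.

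A reader might also infer that normality selects the titre or the visit, or that the pre-test and the omitted strata inflate type I error. Neither holds. Normality governs only the choice of test, and steps 3 and 5 show conservative or negligible effects on error.

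Three further points have force:
- The paired tests do use Day 1, but within an arm. An unpaired test on change from Day 1 is not excluded, though it is not named.
- The size of any gain is assumed. The Secondary Outcome Measures section implies that first-dose recipients may get their second dose during follow-up, so the titre gap could shrink at late visits. A threefold gain in effective sample size needs every favourable extreme at once.
- The Abstract calls the study exploratory, which softens the multiplicity point. It does not remove it, because Study Design claims superiority and one outcome is labelled primary.

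**Conclusion.** The concern holds in limited form. Following the stated list would lose precision. Adjustment for Day-1 titre would lower variance by 9% to 49% at assumed correlations of 0.3 to 0.7, and by more if the dose groups differ in titre. The direction is secure, but the size cannot be derived from the document. Omitting the strata errs on the conservative side; for dose group this supposes that the scheme does balance it. The normality rule matters because of what is estimated, since Mann-Whitney does not test the geometric means, and hardly at all for type I error.

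The open error rate has a different source: two titres and six post-baseline visits with no primary visit and no multiplicity rule. If any of the 12 results could be called primary, the false-positive rate would be roughly 14% to 35% under the assumed correlations. The document does not say that any one would suffice; it leaves the matter unfixed.

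**What to change.** - Replace the selection rule, for the primary outcome, with one linear model on log titre (ANCOVA, or a mixed model for repeated measures). Include Day-1 log titre, dose group and site as covariates, and report a GMT ratio with 95% CI.
- Keep rank tests as sensitivity analyses only.
- State that the Day-1 sample is drawn before the first tablet. Tables 1 and 2 put sampling and dispensing at the same visit without giving an order.
- Name one primary visit, chosen by the sponsor.
- Name one rule for the two titres: either a fixed testing order, or significance required for both. Requiring both needs no alpha split but costs some power.

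The cost is wording in the protocol or SAP, ideally settled before any unblinded data are seen. Day-1 titres, site and dose group are already recorded, so participants carry no added burden.

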# *RT-PCR throat nose swab test will be repeated in participants in case of development of any symptoms during the study duration*.

+ *for female participants*.

*Additional studies on measurement of secretory IgA and T cell responses are planned on a subset of the participants*.

If the vaccinated individual (after first or second dose) contracts COVID 19, then he/she shall be withdrawn from the study and will be treated under the supervision of COVID-19 physician till recovery. The participants who are withdrawn prematurely will be encouraged to continue follow up in a separate group as per the discretion and supervision of the study physician. The latter group will be permitted to use the current protocol methods and analyzed separately. All participants will be monitored for safety, immune response and occurrence of any breakthrough SARS-CoV-2 infection. An interim analysis at the end of 12 week is planned to evaluate the effect of Ashwagandha co-administration on safety and immune response following the first dose of the vaccine. The final analysis of data will be carried out after all the participants have completed the study at the end of 28 weeks.

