#### Withdrawal Criteria

The participants with drug compliance <70% (estimated by recorded tablet consumption), any serious adverse event, or those with positive RT-PCR tests, or clinical symptoms of COVID-19 will be withdrawn from the study. Withdrawn participants who are RT-PCR positive will be referred to a COVID-19 treatment facility for standard care.

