## Strengths and Limitations of this Study

Novel randomized placebo-controlled study of COVID-19 vaccine and immune adjuvant co-administration on safety, immunogenicity, and protection to reduce breakthrough infections.State of art immune assays to measure specific antibodies to SARS-CoV-2 to demonstrate both persistent and late upsurge in immune response.Daily tracking of participants using a study-specific designed mobile app.Participants may be reluctant to donate blood repeatedly for immune assays; compliance with the test drug may be a challenge.

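### Adverse events and infections are tested as crude proportions although withdrawal shortens observation; exits not caused by the counted event bias the comparison if the arms lose people unequally or at different times

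*Protocol article*

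**What the plan says.** The Analysis section names the comparison: Fisher's "exact test or Chi square will be used to test the proportion of participants classified as efficacy failures and those with AE". It adds that "All AEs will be presented as proportion", with a Wilson 95% interval. It names no person-time or time-to-event method.

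Observation can end early by rule. Withdrawal Criteria lists compliance below 70%, and then "any serious adverse event, or those with positive RT-PCR tests, or clinical symptoms of COVID-19 will be withdrawn from the study". Study Design repeats this for infection: a vaccinated person who "contracts COVID 19, then he/she shall be withdrawn from the study". Those withdrawn are "encouraged to continue follow up in a separate group as per the discretion and supervision of the study physician", and that group is analysed separately. Strengths and Limitations expects some difficulty: participants may be unwilling to give blood repeatedly, and "compliance with the test drug may be a challenge".

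Three statements pull the other way. The Analysis section puts all randomised participants in the safety analysis and plans ITT as well as per-protocol analyses. Adverse Events says that safety is also assessed for all withdrawals.

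The efficacy-failure category is not tied to any listed outcome. The primary outcome is an antibody titre. Secondary Outcome Measures lists breakthrough infections as a number of participants, and RT-PCR-confirmed COVID-19 as two proportions with separate windows: Day 1 to week 12 or the second dose, whichever is earlier, and second dose to week 28 or study completion.

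**The concern.** A crude proportion compares the arms fairly when everyone is observed for the planned time, or when observation is lost alike in both arms. This protocol makes neither safe to assume. A participant withdrawn at week 6 counts as one whole person in the denominator but was observed for 6/28, about a fifth, of the planned time.

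The exits that matter are those not caused by the event being counted:

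- low compliance or voluntary dropout, for both outcomes;
- a serious adverse event, which hides a later infection;
- an infection, which hides later adverse events.

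Low compliance and serious adverse events can differ between an active product and placebo. For safety the error then runs in the unwelcome direction: the arm that is less well tolerated, and so loses more people, shows fewer adverse events than it would under full observation. Because the efficacy-failure category is undefined, it is also unclear which infection outcome the test applies to.

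**Working it through.** **Inputs.** From the article: 600 per arm (Sample Size and Power) and 28 weeks of follow-up. The sample size serves only as n here; the point does not depend on how it was derived. The article states no withdrawal, adverse event or infection rate, so all rates below are assumptions, and there is no figure of the plan to reproduce.

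**Model.** Take 28 weeks as one unit of time, with a constant event hazard λ and an independent exit hazard μ:

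- λ = −ln(1 − true 28-week risk); μ = −ln(1 − share leaving);
- observed crude proportion = λ/(λ+μ) × (1 − exp(−(λ+μ))), with all randomised as denominator.

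The rejection rate is that of a two-sided 5% chi-square test (normal approximation, 600 per arm).

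**One case in full: true risk 20% in both arms, loss 10% v 25%.** λ = 0.2231; μ = 0.1054 and 0.2877.

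- 10% loss: 0.2231/0.3285 × (1 − 0.80 × 0.90) = 0.679 × 0.28 = 19.0%.
- 25% loss: 0.2231/0.5108 × (1 − 0.80 × 0.75) = 0.437 × 0.40 = 17.5%.
- Ratio 0.919, false-positive rate 10.7%.

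**No true effect, lower-loss arm at 10%:**

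| Loss in the other arm | Risk ratio (risks 10–40%) | False positives, risk 10% | Risk 20% | Risk 40% |
|---|---|---|---|---|
| 10% | 1.00 | 5.0% | 5.0% | 5.0% |
| 15% | 0.97 | 5.3% | 5.6% | 6.4% |
| 20% | 0.945–0.949 | 6.1% | 7.4% | 10.7% |
| 25% | 0.917–0.923 | 7.6% | 10.7% | 18.5% |
| 30% | 0.888–0.896 | 9.9% | 15.6% | 30.0% |

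At 40% risk and 25% v 10% loss, the observed proportions are 35.2% v 38.1%.

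**Timing.** If all exits fall at week 4, the ratio is about 0.91 for 20% v 10% loss and 0.81–0.82 for 30% v 10%. In the other direction, if half of the adverse event hazard falls in the first 4 weeks, the 18.5% above drops to about 10% and the ratio moves from 0.92 to 0.95.

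**Masking of harm.** Let the arm with 25% loss have a 20% higher adverse event hazard.

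- Base risk 20%: the true ratio is (1 − 0.80^1.2)/0.20 = 1.17; observed 20.5% v 19.0%, ratio 1.08.
- Base risk 40%: the true ratio is (1 − 0.60^1.2)/0.40 = 1.15; observed 40.4% v 38.1%, ratio 1.06.

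**Cross-effect.** If 15% v 5% leave because of infection and the true adverse event risk is equal, the arm with more infections shows an adverse event ratio of about 0.95.

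**Where the mechanism does not act.** A participant withdrawn for a positive RT-PCR is already a counted infection. One withdrawn for a serious adverse event is already a counted participant with an adverse event. Neither exit lowers the proportion for that outcome.

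**The case against.** A reader might infer that whichever arm loses more people will look both safer and better protected. The documents do not support that. An arm that loses more people through positive RT-PCR tests looks worse protected, because each such exit is the event itself. COVID-19 symptoms trigger a repeat swab under the Table 2 footnote, so many of those exits are captured too.

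Nor do the documents show that the Ashwagandha arm would lose more. They give no rates, and the tablets are matched in colour and weight. At 15% v 10% loss the error rate barely moves.

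The safeguards are real but partial. Analysing all randomised participants keeps everyone in the denominator without restoring lost time. Assessing safety in withdrawals does not commit the trial to collecting new events to week 28, and separate analysis keeps what is collected out of the main comparison. For infection, the article does not state the denominator beyond ITT and per-protocol; a per-protocol set would probably drop those below 70% compliance, which changes the problem without solving it.

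It can be said that exposure adjustment belongs in an analysis plan that is not shown, and that a test of proportions suits outcomes listed as numbers and proportions. That would answer a complaint about missing detail. Here, however, the article names the test.

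The alternatives also have limits. They assume non-informative exit, and scheduled swabs 4 to 8 weeks apart leave the dates of asymptomatic infections interval-censored. These are costs of the change and do not favour the crude test, which also ignores why and when people leave.

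**Conclusion.** The concern holds in a limited form. The named test takes no account of observation time, while the protocol's own rules shorten it and set later data apart. Exits not caused by the counted event lower the crude proportion in the arm that loses more, provided that loss is unequal or differently timed.

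Under constant hazards and true risks of 10–40%, the size is modest at 20% v 10% loss (ratio about 0.95, false-positive rate 6–11%) and larger at 25% v 10% (about 0.92, 8–19%). Equal loss with the same timing gives no bias. All of these loss rates are assumed.

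Only secondary outcomes are affected, in a trial that its abstract calls exploratory; the point does not touch the titre primary. The undefined efficacy-failure category is a smaller, separate defect in the same sentence. The change is worth making because it is cheap and because the safety error can hide harm.

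**What to change.** In the Analysis section:

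1. **Infection.** Compare RT-PCR-confirmed infection by time to first infection within each window given under Secondary Outcome Measures, using Kaplan-Meier incidence and a log-rank or Cox comparison stratified by site and entry dose. A single Day 1 to week 28 analysis would not match those windows.
2. **Adverse events.** Compare exposure-adjusted rates (Poisson or negative binomial with log follow-up time as offset), and add Kaplan-Meier incidence of the first adverse event.
3. **Description.** Keep the crude proportions with their Wilson intervals as descriptive results.
4. **Follow-up after withdrawal.** Include whatever is available in the ITT and safety comparisons. This concerns use of the data and leaves the withdrawal rules as they are.
5. **Naming.** Replace the efficacy-failure category with the infection outcome meant.

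The cost is wording and a little more analysis. The daily app, two-weekly calls and visits should supply event and last-contact dates. The downsides are the assumption that exit is non-informative given arm and strata, and interval-censored dates for asymptomatic infections found at scheduled swabs.
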